### Recruitment

Patients are recruited in the respective participating mental healthcare centers. Patients diagnosed with BPD or for whom this is deemed likely are invited to participate in the screening process. After reading and hearing information about the study and signing an informed consent (see Additional file 2, Appendix A), patients will start with the screening process. Not only new referrals can be included, but also patients who are already receiving treatment for mental disorders (except patients receiving ST or DBT).

### Randomization

A central independent research assistant randomizes the patients per center after a final check of the inclusion and exclusion criteria, and after all baseline measures have been completed. Generally, patients will be randomized using computerized covariate adaptive randomization [91–93], taking into account gender and severity of BPD (BPDSI-5 score ≤ 24; BPDSI-5 score > 24). By using this method, the imbalance of baseline characteristics between the treatments will be minimized. Patients are allocated to the treatment group that results in the least imbalance between the treatments with an allocation probability of 0.8 to preserve unpredictability [94]. Groups in both treatments are semi-open which implies that new patients can enter the group if treatment slots are available. Therefore, treatment capacity will be taken into account by using unequal ratios if needed (e.g., 2:1 or 1:3).

In exceptional cases, an alternative randomization method will be used if one or more treatment slots are available in only one condition and there is no available treatment slot in the other condition. To prevent long waiting times for treatment and empty places in the groups, the available treatment slot(s) in one condition will be randomized over 2**k* patients whereby *k* stands for the number of available treatment slots, and randomization is done in the subsample of *k* patients that wait the longest. Randomization over 2**k* patients guarantees unpredictable outcomes. For example, if one treatment slot is available in DBT and there is no available treatment slot in ST at that moment, nor within the foreseeable future, the available treatment slot in DBT will be randomized over two patients waiting for treatment. Sensitivity analyses will be performed by excluding patients that have been randomized using the alternative randomization method.

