## Methods/design

### Design

The study is a multicenter RCT with two active conditions (DBT or ST). The study is set at various Dutch mental healthcare centers accessible through the public health system, including Antes (Rotterdam), GGZ inGeest (Amsterdam), GGZ NHN (Heerhugowaard), GGZ Rivierduinen (Leiden), NPI (Amsterdam), Pro Persona (Ede and Tiel), PsyQ (Rotterdam-Kralingen), and PsyQ/i-psy (Amsterdam). For an overview of the study design, including the enrollment, randomization, interventions, and assessments, see Fig. 1.

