### Sample size

We aim to include 200 participants. Each center intends to recruit at least 18 patients. For the power analysis, we adopted the minimal statistically detectable effect approach [84]. A sample size of 200 will be sufficient to have 80% power to detect moderators of treatment effects that have an effect size of Cohen’s *f* of .20 (small to medium effect size), based on a two-tailed significance level of *p* < .05. In addition, the study has 80% power to detect medium effect-sized (i.e., Cohen’s *f* = .25) moderators of treatment effects, based on a two-tailed significance level of *p* < .01.

Regarding the effectiveness study, with a sample size of *N* = 200 the study is powered at 82% to detect a group difference with a medium effect size of Cohen’s *d* = .50 at a two-tailed significance level of *p* < .05 and assuming a model with center as random effect and an intraclass correlation value of 0.05 corresponding to the center by treatment interaction [85, 86].

Finally, a sample size of *N* = 200 will be sufficient to have 98% power to detect a medium effect size of the mediation effect (*rr* = .09; [87–89]), assuming path *a* (relation between the predictor and mediator) and path *b* (relation between the mediator and outcome measure) both have a medium effect size (*r* = .30), and based on a simplified trivariate mediation model [90].

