#### Clinical effectiveness

Change in the outcome measures and the relative effectiveness of the two treatment conditions will be analyzed using mixed regression so that all available data are used, and taking into account the dependencies among observations nested within individuals nested within centers. Potential center effects are modeled by including a random effect which enables generalization of results outside the trial and maximizes statistical power [211]. Since group sessions in both treatments are offered in a semi-open format, patients will start with group treatment at different time points. One can imagine that patients starting treatment at the same time point are more interdependent compared to patients starting treatment at different time points. Therefore, we will take into account, if needed, the interdependency of patients. The underlying distributions of the mixed regression models will be determined based on the variable type (i.e., scale or nominal) and the distribution of residuals (e.g., normal, gamma, negative binomial).

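### Capacity-driven allocation ratios can vary by centre and over time, but the stated effectiveness model names no term for ratio or randomisation period, nor for the minimisation factors

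*Protocol article*

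**What the plan says.** **Allocation** (protocol article, Randomization). "A central independent research assistant randomizes the patients per center", by covariate-adaptive allocation "taking into account gender and severity of BPD" (BPDSI-5 up to 24 versus above 24), with probability 0.8 for the arm that reduces imbalance. Groups are semi-open, and "treatment capacity will be taken into account by using unequal ratios if needed (e.g., 2:1 or 1:3". When only one arm has a free slot, an alternative method shares the slots over twice as many waiting patients. A sensitivity analysis will exclude patients randomised by that alternative method.

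**Analysis** (Clinical effectiveness). Mixed regression on repeated measures within patients within centres. "Potential center effects are modeled by including a random effect"; the reasons given are generalisation and power. Dependence among patients who start together is handled if needed.

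**Calendar time** (Coronavirus disease (COVID-19) pandemic, repeated in the Discussion). The analysis will control for the pandemic. Whether the variable is a yes/no indicator or an amount of time in treatment is left open until just before analysis. Trial status gives January 2019 to an estimated September 2021 for recruitment.

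**Status of the text** (Statistical analyses). The methods are described as examples, and an updated protocol with the chosen methods is promised before data analysis begins.

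**The concern.** When the ratio depends on free places at a centre at a given moment, randomisation makes the arms comparable only among patients who faced the same ratio: within a centre, and within a period of constant ratio. An analysis that pools over ratio periods compares arms with a different mix of early and late patients. If outcome also drifts over the recruitment years, part of that drift is counted as a treatment effect. A random centre effect does not help here, because the shift happens inside each centre.

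The stated safeguards do not close this gap:

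- The sensitivity analysis concerns the alternative method. Patients randomised at 2:1 or 1:3 under the usual method stay in.
- The pandemic term covers one part of calendar time. If it is coded as time in treatment during the pandemic, it is measured after randomisation and is affected by dropout and early completion, so it cannot stand in for randomisation period.
- The start-time clause deals with correlation between patients, not with a difference in mean outcome between periods.

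A shift in a common direction is conceivable. The Format section gives a group-based treatment phase of up to 12 months in DBT and up to 18 months in ST, with different entry points, so places could free up at different times in the two arms at every centre. That is an inference; the article gives no data on it.

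The minimisation factors are a separate and smaller matter. They are balanced by design, and a model without them does not use that balance.

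**Working it through.** **1. The plan's own figure.** Sample size states "the study is powered at 82% to detect a group difference with a medium effect size of Cohen’s *d* = .50 at a two-tailed significance level", "assuming a model with center as random effect and an intraclass correlation value of 0.05 corresponding to the center by treatment interaction". "We aim to include 200 participants. Each center intends to recruit at least 18 patients". The number of centres in the calculation is not given. The Design section lists eight organisations; one has two sites ("Pro Persona (Ede and Tiel), PsyQ (Rotterdam-Kralingen), and PsyQ/i-psy (Amsterdam"), so nine locations are assumed.

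- Patients per arm per centre: m = 200/9/2 = 11.1.
- Design effect: 1 + (11.1 − 1) × 0.05 = 1.506.
- Effective number per arm: 100/1.506 = 66.4. Standard error: √(2/66.4) = 0.1735.
- Power: Φ(0.50/0.1735 − 1.96) = 82.2%. With 8, 10 and 11 centres: 80.4%, 83.5%, 84.7%.

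The 82% reproduces with 1:1 allocation. If a fixed share q went to one arm throughout, SE² = 2 × 0.05/9 + 0.95/(200q(1 − q)). Power is then 79.2% at 2:1 and 74.5% at 1:3. These are outer cases, since unequal ratios apply only when needed.

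**2. Calendar bias in closed form.** Assumptions, none from the article: ratios are read as DBT:ST (reversing them changes only the sign), half the patients are recruited in each of two periods, all centres shift together, outcome drifts 0.3 SD between periods, and no period or pandemic term is fitted. Bias = difference between arms in the share of early patients × drift.

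| Pattern | DBT early share | ST early share | Difference | Bias at 0.3 SD |
|---|---|---|---|---|
| 1:3 then 2:1 | 0.250/(0.250 + 0.667) = 0.273 | 0.750/(0.750 + 0.333) = 0.692 | 0.420 | 0.126 SD |
| 1:1 then 2:1 | 0.500/(0.500 + 0.667) = 0.429 | 0.500/(0.500 + 0.333) = 0.600 | 0.171 | 0.051 SD |

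Against the target d = 0.50, 0.126 SD is about a quarter (0.126/0.50 = 0.25).

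**3. Simulation.** 9 centres × 22 patients, centre ICC 0.05, two equal periods, true effect zero, 3000 runs, random centre effect fitted at the true ICC.

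| Ratio pattern | Drift (SD) | Bias, random centre only (SD) | Type I error | Bias with period added (SD) |
|---|---|---|---|---|
| 1:3 then 2:1, all centres together | 0.1 | 0.045 | 7% | about 0 |
| same | 0.2 | 0.090 | 10% | about 0 |
| same | 0.3 | 0.124 | 14% | about 0 |
| same | 0.5 | 0.216 | 34% | about 0 |
| Shifts in random directions by centre | 0.3 | about 0 | 6% | about 0 |

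With period in the model, type I error in the synchronised cases returns to about 5-6%.

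**4. Centre.**

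- Ratios that differ by centre but are unrelated to prognosis: with the random centre effect, bias is about 0 and type I error 5.1%.
- Worst case, ratio tied to centre prognosis: 0.135 SD and 15.7% with centre ignored; about 0.07 SD and 7.0% with the random centre effect; about 0 with fixed centre-by-period strata.
- Correlations of 0.4 and 0.7 between ratio and centre prognosis, in a separate simulation of 1000 trials: 0.035 and 0.056 SD with the random centre effect, 0.000 with a within-centre estimator.

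**The case against.** The strongest reply is that the analysis text is openly provisional and that a covariate list is commonly left to the analysis plan. That stands: the article does not exclude ratio, period, gender or severity, and the final model may well include them. But the article fixes a capacity-dependent allocation rule and describes a comparison that does not reflect it. It also already treats slot-driven allocation as needing a sensitivity analysis, and limits that analysis to the alternative method. An announced update is the right place to settle the matter.

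A second reply is that the larger figures need a ratio reversal at all centres at once, plus a drift in outcome. This also stands. Slots open locally, and unsynchronised shifts give about zero bias. The pandemic, the most obvious source of drift, is to be controlled for in some form.

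A reader might go further and infer that the analysis conditions only on a random centre intercept and so leaves arm confounded with both centre and calendar time. The article does not support that:

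- Pandemic control, a start-time clause and one sensitivity analysis are also stated, so the random centre effect is not the only provision.
- The text says a random effect, not an intercept, and the power calculation assumes a centre-by-treatment component.
- Randomisation is within centre, and the random centre effect removes centre confounding or, in the worst case, about halves it.
- Gender and severity are balanced by design, and baseline severity also enters through the change outcome. Omitting them makes standard errors conservative and does not bias the contrast.

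**Conclusion.** The point holds as a gap between the allocation rule and the stated comparison. Following the text as written can leave arm associated with randomisation period, and neither the sensitivity analysis nor the undefined pandemic term reliably covers this.

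The size depends on assumptions for which the article gives no figures. At 0.3 SD drift with synchronised shifts, the bias is about 0.05 SD (1:1 then 2:1) to 0.13 SD (1:3 then 2:1). It is about zero if centres shift independently. Residual centre bias is about zero unless ratio follows centre prognosis, and then at most about 0.07 SD at an ICC of 0.05. The missing minimisation factors are a matter of precision. The stated 82% power is not contradicted.

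**What to change.** In the promised protocol update, for the DBT-ST comparison:

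- Keep centre in the model; a random treatment-by-centre term may stay.
- Add fixed terms for the allocation ratio in force or for randomisation period, defined by what was known at randomisation and not by later time in treatment.
- Adjust for gender and for pre-randomisation BPDSI-5 as a continuous score.
- Record the ratio in force for each patient. The article does not say that it is stored.
- Extend the sensitivity analysis in the Randomization section to exclude patients randomised at unequal ratios as well.
- Run fixed centre effects as a sensitivity analysis, to show whether between-centre information moves the estimate.

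A full fixed grid of centre by period is not needed as the primary model: nine locations and two periods already give 18 cells for 200 patients, and it would abandon the article's reasoned choice of a random centre effect. The cost of the proposal is model wording, one field from the randomisation log and a few degrees of freedom. Design and treatment are unchanged.

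### The alternative randomisation rule contradicts itself: the clause that selects who enters the draw names k patients, where the rest of the paragraph requires 2k

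*Protocol article*

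**What the plan says.** The Randomization section of the protocol article describes a usual method (covariate-adaptive, allocation probability 0.8) and a second route for capacity problems: "In exceptional cases, an alternative randomization method will be used if one or more treatment slots are available in only one condition" and none in the other. For that route it makes four statements about who is in the draw:

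- Size of the draw: "the available treatment slot(s) in one condition will be randomized over 2k* patients whereby *k* stands for the number of available treatment slots".
- Selection of patients, later in the same sentence: "randomization is done in the subsample of *k* patients that wait the longest".
- Rationale, in the next sentence: "Randomization over 2k* patients guarantees unpredictable outcomes".
- Worked example, with one DBT slot open and no ST slot: "the available treatment slot in DBT will be randomized over two patients waiting for treatment".

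The paragraph closes with the planned robustness check: "Sensitivity analyses will be performed by excluding patients that have been randomized using the alternative randomization method". It does not say what happens to the patients in a draw who do not receive a slot.

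**The concern.** The selection clause is not a harmless repetition. The 2k statements fix how many patients are in the draw. The selection clause alone fixes which of the waiting patients they are. Whoever applies the rule needs it, and as written it cannot be applied as a randomisation.

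If it were followed literally, patients would reach an arm because they had waited longest when that arm had room. Waiting time, centre and calendar period would then be tied to treatment, and the next allocation could be foreseen. Waiting is a real feature of this trial: Procedure and assessments provides for repeat measurement at three and six months for patients who cannot yet be randomised. The written rule and the log also carry more weight than usual, because the data management section states that there is no data monitoring committee and no audit.

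A second, conditional issue concerns the sensitivity analysis. If undrawn patients return to the waiting pool, everyone who received an allocation from a given draw is in the open arm. An exclusion that covers only those patients takes people out of one arm according to the result of the draw.

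**Working it through.** **Inputs**, all from the Randomization section: k slots open in one arm; a draw of m patients, with m = 2k (size statement, rationale, example) or m = k (selection clause).

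**Formulas.** If k slots are drawn at random among m patients, each patient's probability of the open arm is k/m, and the number of possible allocations is C(m, k).

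**The plan's own example.** One slot, two patients: m = 2k = 2, probability 1/2 = 0.5, C(2, 1) = 2 allocations. The 2k rule reproduces the example. The k rule would put one patient in the draw and does not.

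**Both readings:**

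| k | Draw of 2k: patients | Probability | Allocations | Draw of k: patients | Probability | Allocations |
|---|---|---|---|---|---|---|
| 1 | 2 | 0.5 | 2 | 1 | 1.0 | 1 |
| 2 | 4 | 0.5 | 6 | 2 | 1.0 | 1 |
| 3 | 6 | 0.5 | 20 | 3 | 1.0 | 1 |
| 4 | 8 | 0.5 | 70 | 4 | 1.0 | 1 |

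With 2k the draw is random for every k. With k it is deterministic for every k, which also contradicts the article's own claim that outcomes are unpredictable.

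**The sensitivity analysis, per draw of 2k patients:**

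- If undrawn patients are assigned to the other arm, k patients in each arm were allocated by this method. Excluding them removes k and k.
- If undrawn patients return to the pool and only drawn patients count as randomised by this method, the exclusion removes k from the open arm and 0 from the other.
- If undrawn patients return to the pool and all 2k are excluded, the numbers removed per arm need not be equal, because undrawn patients may later enter either arm. The exclusion then depends on having entered the draw, which is settled before allocation, and not on its result.

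The article does not say which of these applies.

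**The case against.** The strongest reply is that this is a misprint and the intended design is plain. The 2k rule stands earlier in the same sentence, is repeated with its reason in the next, and is used in the example: three statements against one. A draw among only k patients could not be reconciled with the sentence that contains the clause. A central independent research assistant runs the randomisation, so individual sites do not interpret the text. The route is exceptional, the usual method is untouched, and a sensitivity analysis is already planned.

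Nearly all of this stands. A reader might infer from the clause that the alternative route randomises nobody and sends the longest waiters to whichever arm is open. The article does not support that as a description of the trial's procedure. It supports only that one clause, read alone, would have that effect.

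On the sensitivity analysis, the reply is that slots are randomised over 2k patients, so all 2k can be read as randomised by this method and the planned exclusion may already cover the whole draw. The handling of undrawn patients may also be set out in the full protocol, which is not shown. Both points are fair. A reader might infer that the analysis is one-sided as planned, but that follows only if undrawn patients return to the pool and only drawn patients are excluded. The article states neither.

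What the reply does not remove is a wrong number in an operative allocation rule, in the one clause that selects the patients.

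**Conclusion.** The paragraph contradicts itself, and the selection clause is wrong as written: it gives allocation probability 1.0 where the rest of the paragraph gives 0.5. The likeliest explanation is a slip for 2k. The article cannot show what was done in practice, so confirmation is needed, but it gives no reason to assume that patients were allocated without randomisation.

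The effect on the trial cannot be sized. The article does not state how many of the planned 200 patients enter by this route and calls such cases exceptional. If past draws used 2k, the correction is to wording only. The point about the sensitivity analysis is a clarification that depends on how undrawn patients are handled. Overall this is a minor to moderate correction.

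**What to change.** 1. Change the selection clause so that it names the 2k longest-waiting patients, in line with the size statement, the rationale and the example.
2. Confirm from the randomisation log that every past draw by this route included 2k patients, and report the number of draws and patients involved.
3. State that the planned sensitivity analysis excludes all 2k patients of each draw, drawn and undrawn. State also whether undrawn patients return to the pool or are assigned to the other arm. An identifier for each draw in the log makes this workable.

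The cost is one corrected clause, one or two added sentences, a log check and an identifier. The protocol update that the Statistical analyses section promises before data analysis is a natural place for the text. No change to the design or the sample size is needed.

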### Procedure and assessments

Patients with BPD or suspected of BPD are invited to the screening process by the research assistant or intake staff member. After providing written informed consent, patients are assessed for eligibility to participate in the study based on the inclusion and exclusion criteria. First, to assess DSM-5 syndrome disorders, the SCID-5-S is administered. The SCID-5-PD will also be administered in case the SCID-5-PD is not part of the standard intake procedure of the mental healthcare center. Second, the BPDSI-5 and a screening interview to assess the motivation and availability of the patient are conducted. A simple “yes” answer to the questions posed by the interviewer (e.g., “Are you motivated and available for treatment, including individual and group sessions?”) is not sufficient. Patients need to elaborate on their answers and follow-up questions are asked if needed. Patients who are eligible for participation will be invited for the baseline assessment, including interviews and computer-based self-report questionnaires, and intake staff members will fill out a questionnaire (i.e., intake questionnaire; see the Measures section) about these patients. After completing the baseline assessment, patients will be randomized as soon as treatment slots become available. Patients will be informed that they have been allocated to one of the treatment conditions, but the name of the treatment will not be communicated to the patient until the first treatment session. If patients cannot be randomized within several months after completing the baseline assessment because of unavailability of treatment slots, the BPDSI-5 will be re-assessed after three months and the BPDSI-5 and cost interview will be re-assessed after six months.

After the treatment phase has started, patients are reassessed every six months during the two years of treatment. These assessments are a combination of interviews and computer-based self-report questionnaires. In addition, a selection of measures are also assessed every three months, by computer-based self-report questionnaires. After end of the treatment, two follow-up assessments (six and 12 months after end of the treatment) will be administered. An overview of the measures is presented in Table 1. Candidate predictors of (differential) treatment response that are assessed only once at baseline are not included in Table 1. These measures can be found in the Measures section.

